**I. Research Background**

Continuous renal replacement therapy (CRRT) is an effective treatment for acute kidney injury (AKI). Due to its continuous nature, mildness, and minimal impact on hemodynamics, it has been widely applied in clinical practice. The efficacy of CRRT is not only related to the treatment modality but also closely associated with the lifespan of the filter. A longer filter lifespan means fewer replacements and a lower risk of complications, thereby enhancing the safety and cost-effectiveness of the treatment.

Anticoagulation is a conventional practice in CRRT to prevent filter clotting and prolong filter lifespan. However, the use of anticoagulants carries a risk of bleeding, especially in patients with a tendency to bleed. Therefore, anticoagulant-free strategies have gained increasing attention, aiming to reduce anticoagulant-related complications while maintaining filter function and lifespan.

Blood flow rate is a critical operational parameter in CRRT, influencing both filter clotting risk and treatment efficacy. A higher blood flow rate can reduce the dwell time of blood in the filter, thereby lowering the risk of filter clotting and thrombus formation. However, for hemodynamically unstable patients, a higher flow rate may lead to decreased blood pressure and reduced cardiac output. An appropriate blood flow rate can ensure effective filtration and clearance of metabolic waste, thereby improving renal function. Thus, studying the impact of blood flow rate on filter lifespan in anticoagulant-free CRRT is of significant importance for optimizing treatment protocols, reducing medical resource consumption, and improving patient outcomes.

This study aims to investigate the impact of different blood flow rate settings on filter lifespan in anticoagulant-free CRRT, in order to provide more precise treatment parameters for clinical practice and improve the therapeutic outcomes for AKI patients.

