**IV. Case Selection**

1. **Inclusion Criteria**
   1. Patients undergoing CRRT;
   2. Age 18 years or older;
   3. No anticoagulant used during CRRT;
   4. Informed consent provided by the patient or their legal guardian/agent.
2. **Exclusion Criteria**
   1. Patients with severe coagulation disorders or undergoing anticoagulant therapy;
   2. Patients receiving intermittent renal replacement therapy (IRRT) or other non-CRRT treatments;
   3. Pregnant women.
3. **Criteria for Study Termination**
   1. **Safety Issues:** Serious adverse events: If during the study, the incidence of serious adverse events related to treatment such as hypotension, malignant arrhythmias, or death is significantly higher in one group compared to the other two groups, or exceeds the predefined safety threshold, consideration should be given to terminating that group's study. The safety threshold is set based on data from similar previous studies and the opinions of clinical experts to ensure patient safety. For example, if the incidence of bleeding events exceeds 10% and is 5% or more higher than the other groups; the incidence of thrombotic events exceeds 5% and is 3% or more higher than the other two groups; the incidence of infectious events exceeds 15% and is 5% or more higher than the other groups; the incidence of cardiovascular events exceeds 8% and is 4% or more higher than the other two groups [2,3].
   2. **Inadequate Effectiveness:** Interim analysis: Interim analysis will be conducted after 50% of the patients have been enrolled, performed by an independent statistician who is blinded to treatment allocation.
   3. **Interim Analysis Objectives:** To assess filter lifespan in different blood flow rate groups, compare filter blockage rates among groups, and evaluate the incidence of adverse events.
   4. **Interim Analysis Indicators:** Primary outcome measure: Filter lifespan (hours); Secondary outcome measures: Filter clotting rate, incidence of adverse events (bleeding, thrombus formation, etc.).
   5. **Interim Analysis Method:** Kaplan-Meier survival analysis will be used to assess filter lifespan, and the Log-rank test will be used to compare differences in filter lifespan among different groups. The chi-square test will be used to compare differences in filter blockage rates and adverse event incidence among groups.

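### The example safety thresholds ask one arm to stand above both others, so on the natural reading harm shared by 200 and 250 mL/min usually raises no flag

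*Protocol*

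**What the plan says.** Item 1 of the termination criteria (Protocol, section IV) has two triggers joined by *or*. The serious-event incidence in an arm either "is significantly higher in one group compared to the other two groups, or exceeds the predefined safety threshold". Four numerical examples of the threshold follow:

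- Bleeding: "if the incidence of bleeding events exceeds 10% and is 5% or more higher than the other groups".
- Thrombosis: "the incidence of thrombotic events exceeds 5% and is 3% or more higher than the other two groups".
- Infection: "the incidence of infectious events exceeds 15% and is 5% or more higher than the other groups".
- Cardiovascular: "the incidence of cardiovascular events exceeds 8% and is 4% or more higher than the other two groups".

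In each, the level and the gap are joined by *and*, so passing the level alone never flags an arm. The text does not say whether the gap is over each remaining arm or over the two taken together. The consequence of a flag is soft and concerns one arm: "consideration should be given to terminating that group's study".

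Items 2 to 5 add one interim analysis at half enrolment, with a chi-square comparison of adverse events across the three arms. Item 7 sends the results to a DSMB. On direction of harm, section I says that "for hemodynamically unstable patients, a higher flow rate may lead to decreased blood pressure and reduced cardiac output".

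**The concern.** The three arms are ordered levels of one exposure: 150, 200 and 250 mL/min. If faster flow causes harm, two plausible patterns are a plateau (200 and 250 equally affected) and a gradient. A rule that looks for one arm standing clear of both others is built for a single outlier. In a plateau, each harmed arm is the reason the other is not flagged, and in a shallow gradient the middle arm shields the top one. The significance trigger, "is significantly higher in one group compared to the other two groups", has the same one-against-two structure.

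These are the only numerical safety thresholds in the protocol, so the DSMB may treat the absence of a flag as reassurance.

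**Working it through.** **Numbers per arm.** The protocol plans 153 per group; 153 / 0.95 = 161.05, rounded up to 162, and 3 × 162 = 486. Half of 486 is 243, or 81 per arm at the interim. These figures reproduce. The protocol states no operating characteristic for the thresholds and no expected event rates, so all incidences below are assumptions. Patients are taken as independent. The abstract counts 486 cases but the sample-size section counts 486 filters, so there may be fewer than 162 patients per arm.

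**The rule applied to observed rates (gap over each other arm).**
- Bleeding 5/15/15%: the 200 and 250 arms are both above 10% and 10 points above 150, but 0 points above each other. No flag.
- Cardiovascular 6/9.5/13%: the 250 arm is above 8% and 7 points above 150, but 13 − 9.5 = 3.5 points above 200, short of 4. No flag.

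**Probability of a flag, shared harm.** Take true bleeding of 5/15/15%. A flag depends almost entirely on a chance difference of at least 5 points between the two harmed arms. The standard error of that difference is √(2 × 0.15 × 0.85 / n).
- n = 81: SE = 5.61 points. The gap needs 5 events (0.05 × 81 = 4.05). With continuity correction, 4.5/81 = 5.56 points, z = 0.99, two-sided probability about 32%.
- n = 162: SE = 3.97 points. The gap needs 9 events (0.05 × 162 = 8.1). With correction, 8.5/162 = 5.25 points, z = 1.32, probability about 19%.

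Detection falls with more data because chance gaps between equally harmed arms shrink. Two arms cannot each exceed the other, so a flag names only one.

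**Results over scenarios.** Exact binomial sums and simulation agree on the probability that some arm is flagged:

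| Assumed incidence, 150/200/250 | Step 200 to 250 against gap (points) | 81 per arm | 162 per arm |
|---|---|---|---|
| Bleeding 5/15/15% | 0 against 5 | 32% | 19% |
| Cardiovascular 6/13/13% | 0 against 4 | 39% | 28% |
| Cardiovascular 8/10/12% | 2 against 4 | 32% | 25% |
| Cardiovascular 6/9.5/13% | 3.5 against 4 | 44% | 44% |
| Bleeding 5/10/15% | 5 against 5 | 46% | 47% |
| Cardiovascular 4/8/12% | 4 against 4 | 48% | 50% |
| Cardiovascular 4/10/16% | 6 against 4 | 64% | 71% |
| Bleeding 5/5/15% (single outlier) | 10 against 5 | 74% | 88% |
| Cardiovascular 8/8/8% (no difference) | 0 against 4 | 20% | 10% |

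**Gap over the average of the other two arms.** By exact enumeration, bleeding 5/15/15% now flags some arm in about 83% (81 per arm) and 85% (162). This reading also flags more when nothing differs: cardiovascular 8/8/8% in about 41% and 22%, against 20% and 10% above.

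**Other routes.** For cardiovascular 4/12/12%, the significance trigger (higher than each other arm at 0.05) is met in 4 to 5% of trials. The combined flag rate stays at the threshold rule's own 39% and 26%. The three-arm chi-square is positive for bleeding 5/15/15% in 56% at 81 per arm.

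**Adding a trend test.** With scores −1, 0, 1, Z = (p250 − p150) / √(2p̄(1 − p̄)/n), positive if |Z| > 1.96. Either the existing gap trigger or the trend test fires as follows (81, then 162 per arm):
- Bleeding 5/15/15%: 67% and 88%.
- Cardiovascular 6/13/13%: 54% and 67%.
- Cardiovascular 8/8/8%: 22% and 12%.

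Used alone at 81 per arm, the trend test finds cardiovascular 6/13/13% in 29%, below the present rule's 39%. It should therefore supplement that rule, not replace it.

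**The case against.** Much of the case on the other side stands.

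- The thresholds are offered as examples and lead only to consideration, so the DSMB can act without a flag.
- The interim chi-square needs no single outlier and, for bleeding 5/15/15%, does about as well as a trend test (56% against 52% at 81 per arm). It is specified for only one look, whereas item 1 applies throughout. Item 6, the other arm-stopping rule, also requires shorter filter life. The center's earlier data show longer life at 250 than at 200 (35.51 against 28.09 hours), so item 6 is unlikely to catch harm at the top flow.
- The figures are per event class. If all four classes were raised together in both higher-flow arms (each to its level plus its gap) and were independent, at least one rule would flag in 86% (81 per arm) and 70% (162).
- The averaged reading is not excluded by the text and would flag most shared harm. That is a reason to state the comparator.

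A reader might infer two stronger points that the protocol does not support. One is that any harm rising with flow usually escapes. The table shows the opposite once the 200-to-250 step clearly exceeds the gap. The other is that the protocol expects harm to rise with flow. Section I speaks only of a possible hemodynamic effect in unstable patients and says faster flow lowers clotting risk. It links neither bleeding nor infection to flow, so the bleeding rates here only illustrate the rule.

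**Conclusion.** The point holds in limited form. If the gap is over each other arm, which is the natural reading, harm shared by 200 and 250 mL/min goes unflagged in 61 to 81% of trials in the two main scenarios (100 − 39 and 100 − 19). Detection worsens with more data, and at most one of the two harmed arms is named. Graded harm is missed about half the time or more only when the step from 200 to 250 is at or below the gap. On the averaged reading most shared harm is flagged, so an unstated comparator moves detection of bleeding 5/15/15% at 162 per arm from 19% to about 85%.

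These sizes rest on assumed incidences, independent patients, and 81 or 162 patients per arm. The rule is advisory and has a partial safeguard at the interim, so this is a weakness worth correcting and does not leave the trial without safety oversight. Whether the absolute levels are appropriate is not judged here.

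**What to change.** In item 1 of the termination criteria, keep the absolute levels and the existing gap trigger, and make three changes:

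1. State whether the gap is over each other arm or over the two combined, with the same wording for all four event classes.
2. State that two arms above the level can both be referred to the DSMB.
3. Add, without substituting it for the gap trigger, a test for trend across 150/200/250 mL/min for each event class, two-sided at 0.05, as a further trigger for DSMB consideration.

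What is done with a flagged arm stays with the DSMB.

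The cost is two or three sentences and one extra test on data already collected. When the arms are equally safe, the trend test is positive in 5% of looks per event class, or up to 1 − 0.95⁴ ≈ 19% over four independent classes. Part of this is not new, because the present rule already flags many of those trials: for cardiovascular 8/8/8% the total rises only from 20% to 22% at 81 per arm and from 10% to 12% at 162.

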   - **Sample Size Calculation:** The primary outcome measure of this study is filter lifespan. Therefore, filter consumption quantity is selected for sample size calculation. Based on retrospective and prospective cohort study data from our center, the smallest difference in filter lifespan was observed between the 200 mL/min and 250 mL/min blood flow rate groups. Thus, the maximum possible sample size can be calculated based on the lifespan difference between these two groups. Previous study results showed that the average filter lifespan was 28.09 ± 21.15 hours in the 200 mL/min blood flow rate group and 35.51 ± 17.97 hours in the 250 mL/min blood flow rate group. With a significance level (α) set at 0.05 and power at 0.90, the software PASS (Power Analysis and Sample Size Software) version 15 was used to calculate a sample size of N = 153 per group. Considering a dropout and refusal rate of 5%, the final number of filters required per group is at least 162, totaling at least 486 filters.
2. **Research Methods**

Patients undergoing CRRT at West China Hospital who meet the inclusion and exclusion criteria will be randomly divided into three groups: low blood flow rate group, medium blood flow rate group, and high blood flow rate group. The international standard blood flow rate for anticoagulant-free CRRT is 250 mL/min, while the standard blood flow rate for anticoagulant-free CRRT at our center is 200 mL/min. For hemodynamically unstable patients or those with high circuit pressure, our center reduces the blood flow rate to 150 mL/min based on experience, which is consistent with previous studies defining 150 mL/min as the low blood flow rate group [1]. Therefore, we define 150 mL/min, 200 mL/min, and 250 mL/min as the low, medium, and high blood flow rate groups, respectively.

- **Low Blood Flow Rate Group:** Adjust the CRRT blood flow rate to 150 mL/min.
- **Medium Blood Flow Rate Group:** Adjust the CRRT blood flow rate to 200 mL/min.
- **High Blood Flow Rate Group:** Adjust the CRRT blood flow rate to 250 mL/min.

The remaining CRRT prescription and parameter adjustments will be determined based on the patient's actual condition, experienced clinical physicians, and CRRT specialists. If during CRRT, high blood flow rate causes high vascular access pressure and requires a reduction in blood flow rate, the following principles will be followed:

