   6. If the interim analysis results show that the filter lifespan in any group is significantly lower than the other groups (P < 0.05), and the incidence of adverse events is significantly increased, enrollment of patients in that group will be terminated. If there is no significant difference in filter lifespan among all groups (P > 0.05), and no significant difference in adverse event incidence, the study will continue until all patients have been enrolled.
   7. The statistician will report to the independent Data and Safety Monitoring Board (DSMB), which will review and assess the interim analysis data and provide recommendations to the researchers on whether to continue, modify, or terminate the study [4][5].
   8. **Achievement of Statistical Significance:** If the interim analysis shows a significant difference in filter lifespan among different blood flow rate groups (P < 0.05), and this difference is sufficient to prove the primary research hypothesis, the study may be terminated early.
   9. **Participant Request to Withdraw:** If a participant requests to withdraw from the study.

**Termination Procedure:** Upon receiving the DSMB's recommendation, the study leader should immediately suspend enrollment of new patients and notify all research centers; inform the Institutional Review Board (IRB) and relevant regulatory authorities, providing the reasons for termination and the interim analysis results; provide appropriate follow-up treatment and follow-up for patients already enrolled.

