**XI. Statistical Analysis**

SPSS software (version 27.0, SPSS Inc., USA) and R version 4.2 (R Foundation for Statistical Computing, Vienna, Austria) will be used for data analysis.

1. **Descriptive Statistical Analysis:** Basic characteristics of the study sample will be described, including demographic features, laboratory indicators, underlying diseases, etc. Descriptive statistical analysis will also be conducted on filter lifespan, filter performance indicators, and changes in patient physiological parameters across different blood flow rate groups, including mean values, standard deviations, medians, etc.
2. **Survival Analysis:** Survival analysis methods (e.g., Kaplan-Meier curves) will be used to compare differences in filter lifespan among different blood flow rate groups. Cox proportional hazards models will be employed to analyze factors that may affect filter lifespan, such as blood flow rate, patient age, underlying diseases, etc.
3. **Analysis of Variance (ANOVA):** Differences in filter performance indicators among different blood flow rate groups will be analyzed using ANOVA.
4. **Safety and Adverse Event Analysis:** The incidence of adverse events (e.g., thrombus formation, bleeding complications) among different blood flow rate groups will be compared using chi-square tests or Fisher's exact tests to assess the safety of CRRT treatment at different blood flow rates.
5. **Clinical Outcome Analysis:** Appropriate statistical methods will be used to compare clinical outcomes, such as renal function recovery, survival rate, and hospital stay duration, among different blood flow rate groups.

A P-value of less than 0.05 will be considered statistically significant.

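### The interim efficacy stop and the final test both use P < 0.05, so the overall false-positive rate can reach about 8.4% rather than 5%

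*Protocol*

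**What the plan says.** All of this is in the protocol.

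- **Timing.** Section IV, Criteria for Study Termination, item 2: "Interim analysis will be conducted after 50% of the patients have been enrolled".
- **Test.** Item 5 of the same list: Kaplan-Meier curves, and "the Log-rank test will be used to compare differences in filter lifespan among different groups". Item 4 names filter lifespan as the primary measure at this look.
- **Efficacy stop.** Item 8 opens with the trigger: "If the interim analysis shows a significant difference in filter lifespan among different blood flow rate groups (P < 0.05"). It then adds a second condition and makes the stop optional: "and this difference is sufficient to prove the primary research hypothesis, the study may be terminated early".
- **Arm closure.** Item 6 closes enrolment to a group if "filter lifespan in any group is significantly lower than the other groups (P < 0.05") and adverse events are also significantly increased.
- **Otherwise continue.** Item 6 adds that, with no significant difference in lifespan or in adverse events, "the study will continue until all patients have been enrolled".
- **Review.** Item 7 sends the interim results to an independent data and safety monitoring board, which makes a recommendation.
- **Final level.** Section XI: "A P-value of less than 0.05 will be considered statistically significant".
- **Design level.** Section III, sample size: "With a significance level (α) set at 0.05 and power at 0.90". No allowance for an interim look is mentioned.

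**The concern.** The same primary outcome can be declared significant on two occasions, each time at the full 0.05. A trial with no true difference therefore has two chances of a positive result, and the two together exceed the 5% on which the sample size was based.

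This does not depend on something that may be in an unseen statistical analysis plan. The protocol itself states both thresholds, so an analysis plan with a proper boundary would contradict item 8 as written.

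Two further things are at stake. A trial stopped because a half-sample result crossed P < 0.05 tends to overstate the effect. It would also end with about half the planned data for the secondary objectives on adverse events, hemodynamics and clinical outcomes.

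**Working it through.** **Inputs from the protocol.** One interim look at 50% of patients; P < 0.05 at the interim (section IV, item 8) and at the end (section XI); three groups, 1:1:1; lifespan 28.09 ± 21.15 h at 200 mL/min and 35.51 ± 17.97 h at 250 mL/min; 153 per group.

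**Assumptions.** Tests are two-sided. The information fraction t at the look is 0.5, with 0.4 to 0.6 shown because half the patients need not mean half the information. Every interim P < 0.05 counts as positive; this is relaxed in step 4.

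**1. The plan's own figure.** With difference 35.51 − 28.09 = 7.42 h and variance sum 21.15² + 17.97² = 770.24, n = 770.24 × (1.960 + 1.282)² / 7.42² = 147 per group. A Mann-Whitney adjustment (× π/3) gives 153.9, close to the stated 153; the protocol does not name the test used. 153 / 0.95 rounds up to 162, and 3 × 162 = 486. These figures contain no interim allowance. The small gap between 147 and 153 does not affect this point.

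**2. One pair of groups (1 df).** Under the null, Z₁ (interim) and Z₂ (final) are bivariate normal with correlation √t.

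Rate = 1 − P(|Z₁| < 1.96 and |Z₂| < 1.96)

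**3. Three-group log-rank (2 df).** The critical value is 5.991 at each look. Given an interim score of length r, the final statistic divided by (1 − t) is noncentral chi-square on 2 df with noncentrality t·r²/(1 − t).

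Rate = 0.05 + ∫ from 0 to √5.991 of r·exp(−r²/2) · P[χ²₂(t·r²/(1 − t)) > 5.991/(1 − t)] dr

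| Information fraction | 1 df | 2 df |
|---|---|---|
| 0.4 | 8.63% | 8.73% |
| 0.5 | 8.31% | 8.41% |
| 0.6 | 7.96% | 8.06% |

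A simulation of 2,000,000 null trials gave 8.41% for the 2-df case at t = 0.5.

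**4. If only some significant interims end the trial.** Let s be the share that do, unrelated to how strong the result is, with the final test at 0.05 otherwise. The rate is then about 5.0% + s × (8.4% − 5.0%). For s = 0.5 this is 6.7%; for s = 0.75 it is 7.6%.

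**5. Illustration of how often the rule would bite.** Treat lifespan as a normal mean difference, 200 versus 250 mL/min, with the protocol's inputs. The expected full-sample z is 7.42 / √(770.24/153) = 3.307. At half the information it is 3.307 × √0.5 = 2.338.

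- Chance of crossing 1.96 at the interim: 1 − Φ(1.960 − 2.338) = 0.647.
- Mean z given crossing: 2.338 + φ(0.378)/0.647 = 2.912. The overstatement is 2.912 / 2.338 = 1.25.

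**6. Boundaries that restore the level (t = 0.5).**

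| Interim / final P | 1 df | 2 df |
|---|---|---|
| 0.001 / 0.05 (Haybittle-Peto) | 5.02% | 5.03% |
| 0.003 / 0.049 (O'Brien-Fleming-type spending) | 5.00% | 5.01% |

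In the setting of step 5, the chance of crossing at the interim falls from 0.65 to 1 − Φ(3.291 − 2.338) = 0.17 with the first boundary, and to 1 − Φ(2.968 − 2.338) = 0.26 with the second.

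**The case against.** The best defence is that item 8 is not an automatic stop. It needs a second condition, that the difference suffices to prove the primary hypothesis; it only permits termination; and a monitoring board reviews the data. A reader might infer from the two thresholds that the error rate simply is above 8%. The protocol does not support that: 8.3% to 8.4% is the rate when every significant interim is called positive. If the board let through only very strong results, the excess could be small. What does not stand is that the condition controls the error. It has no numerical definition, the primary objective states no threshold that could supply one, and the only criterion given to the board is P < 0.05.

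Three other stronger readings should also be set aside.

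- **A rate near 19.5%.** This results from testing all three pairs at 0.05 at both looks. Unadjusted pairwise testing already gives about 12.2% at a single look, and the protocol does not specify three unadjusted pairs as the efficacy rule. It describes a comparison among the groups.
- **Items 6 and 8 prescribe different actions for the same result.** Their triggers differ: item 6 needs shorter lifespan and more adverse events, item 8 a lifespan difference that is judged sufficient. What stands is narrower: one interim result can meet both, and no precedence is given.
- **The efficacy boundary should also govern item 6.** Item 6 closes an arm that does worse on lifespan and on adverse events; it makes no efficacy claim. A stricter lifespan threshold there would make such an arm harder to close. Nothing in the error-rate argument calls for it.

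The 65% and 1.25 in step 5 are illustrations only. They use a two-group comparison of means, whereas the interim test is a log-rank test, and filters also come off at 72 hours or for reasons other than clotting (section VI).

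**Conclusion.** The point holds and should be corrected before the interim analysis. The protocol offers the full 0.05 twice on its primary outcome. If every interim P < 0.05 is treated as positive, the overall two-sided rate is about 8.3% (one pair) to 8.4% (three groups) at an assumed information fraction of 0.5, and about 8.0% to 8.7% across fractions 0.6 to 0.4. Selective stopping would give a lower figure, but the rate exceeds 5% as soon as a bare interim P < 0.05 can end the trial. Under the protocol's own planning values such a crossing would be common. The overlap of items 6 and 8 is a secondary matter of clarity.

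**What to change.** In section IV, item 8, replace P < 0.05 with a group-sequential efficacy boundary for the primary lifespan test. Either of these would do:

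- Haybittle-Peto: P < 0.001 at the interim, 0.05 at the final analysis. Section XI can stay as it is.
- An O'Brien-Fleming-type spending boundary: about 0.003 at the interim and 0.049 at the final analysis. The level for the primary test in section XI then changes to match.

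If the look does not fall at half the information, the spending boundary should be recalculated at the actual fraction. State whether the test is the overall three-group log-rank, and either define the condition about proving the hypothesis or delete it.

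Separately, reconcile items 6 and 8 by saying which governs when an interim result meets both. No change to the arm-closure threshold in item 6 is proposed.

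The cost is a short protocol amendment, with the monitoring board's instructions brought into line. The final level stays at 0.049 to 0.05, so power loss is negligible and the sample size need not change. The price is a lower chance of stopping early, as shown in step 6 of the working.
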